**Figure 3 F3:**
[figure not shown]
Flow of participants through the PEP4LEP study.

### Community-based skin camp intervention

A skin camp will be organised when a patient with leprosy is diagnosed by inviting approximately 100 people from the same community (table 1) living in the surrounding area (field definition: inhabitants from the 20 closest houses). Community contacts from outside of the 20 closest households who attend a skin camp can still receive skin screening or referral, but will not be given SDR-PEP. Health camps are designed to bring specialised care closer to the community, thus expanding healthcare access.^37^ Besides providing preventive and curative treatment, these camps often also play a significant role to create awareness.^38^ Community ‘skin health camps’ have been proposed as an effective way to screen for leprosy and other NTDs.^7 39^ Skin camps are organised at the community level and in close collaboration with community leaders and local organisations.^37 40^ In a skin camp, health staff screen individuals for skin diseases and then treat or refer patients if necessary. Assistance from a dermatologist (or, if none available, a senior health staff member with sufficient dermatology experience) is vital.^41^ A key advantage of this community intervention is that the identity of the person affected by leprosy can be protected since no individual disease disclosure is needed. This non-disclosure approach is of utmost importance, as people affected by leprosy are often stigmatised and discriminated against and are therefore reluctant to share their disease status.^42–44^ Moreover, including a wider group of contacts and using an integrated skin diseases approach may overcome the frequently negative associations with leprosy that can prevent people from participating in a leprosy-related intervention.^19^ Including approximately 100 contacts per identified patient with leprosy in the PEP4LEP skin camps is in-line with the risk profiles of the contact groups and is operationally manageable to conduct within 1–2 days, also when using time slots to prevent crowding, taking COVID-19 into consideration.^6 13 34 36 38 39 45–47^

### Health centre-based intervention for household contacts

In the second intervention, newly detected patients with leprosy will be asked to invite their household contacts to visit a health centre to have their skin screened and, if eligible, to be offered SDR-PEP. Clustering of the disease within households is commonly seen.^6 47 48^ Household contacts are defined as living under the same roof as the index patient with leprosy for a minimum of 3 months (table 1).^13 49 50^ To prevent re-infection within a household and for operational management reasons, contacts need to visit the health centre within 3 months after the index patient was included, which is also in-line with contact tracing interventions in literature.^51^ Around six household contacts per patient are expected to visit the health centre for screening.^13^ Previous studies showed that patients with leprosy are usually willing to disclose their leprosy diagnosis to their household members to facilitate screening and prophylaxis, but they are often reluctant to share this information with neighbours or other social contacts.^42–44^

### Integrated skin screening

For contact screening in both interventions, an integrated skin diseases approach—also called common skin screening approach—will be used to diagnose common skin diseases (eg, eczema), skin conditions related to HIV/AIDS (eg, Kaposi’s sarcoma) and skin-NTDs (eg, leprosy). ‘Integration’ in this context refers to combined screening for a minimum of two diseases at the same time in the same communities.^52^ In the PEP4LEP project, free topical treatment for the most frequently diagnosed skin diseases will be provided as well as referral advice, in-line with WHO and national medical guidelines.^53–57^ The screening for signs and symptoms of skin diseases, as well as the chemoprophylaxis distribution, will follow standard operating procedures (SOPs) in which the eligibility criteria for SDR-PEP are clearly stated. In both interventions, the integrated skin diseases approach will be used and supported by the SkinApp, an mHealth tool developed by NLR and Erasmus University Medical Center (Erasmus MC).^30 31^ The SkinApp will support peripheral health workers in recognising and treating signs and symptoms of skin diseases, including skin-NTDs like leprosy.^30 31^ A senior health staff member with sufficient dermatology experience (preferably a dermatologist) will attend in person or via secure medical messaging via the application (app) Siilo.^58^

### Post-exposure prophylaxis

Chemoprophylaxis with SDR-PEP has been adopted in the 2018 WHO ‘Guidelines for the diagnosis, treatment and prevention of leprosy’.^4^ The SDR-PEP dosages used in this project (table 2) are consistent with these WHO guidelines, the 2020 published WHO document ‘Leprosy/Hansen disease: Contact tracing and post-exposure prophylaxis. Technical guidance’ and the LPEP programme.^4 7 13^

**Table 2 T2:** PEP4LEP single-dose rifampicin dosages^4 7 13^

Age and body weight of contact	Rifampicin dosage
≥15 years	600 mg
10–14 years	450 mg
6–9 years and body weight of ≥20 kg	300 mg
≥2 years old and body weight between 10–20 kg	150 mg

Contacts who are temporarily ineligible to receive SDR-PEP (eg, because of pregnancy, table 1) will receive skin screening and an SDR-PEP voucher, useable in an affiliated PEP4LEP health centre when becoming eligible (eg, after giving birth). Contacts receiving SDR-PEP will also receive an SDR-PEP Red Card to keep in their homes. This card indicates that the person has received SDR-PEP for leprosy prevention and is ineligible to receive this again within the next 2 years. These methods were previously used as part of the LPEP programme in Tanzania.^13^ In PEP4LEP, serious adverse events (SAEs) will be reported and followed up according to national and PEP4LEP guidelines (see ethical section).^59^

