Exclusion criteria	Index patient or parents/legal guardians unable to understand the purpose and risks of participating in the PEP4LEP study.	Contact or parents/legal guardians unable to understand the purpose and risks of participating in the PEP4LEP study. Age <2 years and/or <10 kg of weight.* Pregnancy.* Receiving or having received rifampicin for any reason in the last 2 years. Known allergy to rifampicin. History of liver or renal disorders. Individuals with leprosy and those who have possible signs and/or symptoms of leprosy (eg, leprosy-like skin lesions or nerve manifestations) until their disease status has been clarified.† Individuals with possible signs and/or symptoms of TB (cough for more than 2 weeks or cough in known patients with HIV/AIDS, night sweats, unexplained fever, weight loss) until their disease status has been clarified.‡^113^ Individuals with possible signs and/or symptoms of COVID-19 (self-assessed temperature ≥38°C, respiratory or cold-like symptoms, sudden loss of smell/taste) or possible contact with a patient with COVID-19 in the past 14 days.‡^33–36^

*A voucher will be given for repeated skin screening and SDR-PEP. This can be used in a PEP4LEP affiliated health centre when this person becomes eligible (eg, after giving birth).

†If referral was needed and no leprosy is detected, repeated skin screening and SDR-PEP can be provided in a PEP4LEP affiliated health centre.

‡Skin screening and SDR-PEP can only be provided in a PEP4LEP affiliated health centre after the contact is tested negative for COVID-19/TB (according to national guidelines).^33–36^

MDT, multidrug therapy; SDR-PEP, single-dose rifampicin post-exposure prophylaxis; TB, tuberculosis.

The target population for the feasibility component of this study as well as the other research objectives, consists of various stakeholders, including: (index) patients, household contacts, community contacts, community leaders, health workers, community health volunteers and health policy decision-makers. If applicable, contacts refusing to receive skin screening and/or SDR-PEP, but who are willing to participate in the qualitative component will also be included in the project, contributing to the acceptability component of the study.

The exclusion criterion for these stakeholders is refusal to provide informed consent to participate.

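### The rifampicin dose table has no row for children aged 2–5 years above 20 kg and two rows for contacts aged 10–14 years weighing 10–20 kg

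*Protocol article*

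**What the plan says.** Two tables in the protocol article bear on this.

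- **Table 1** (Participants and eligibility criteria) lists among the contact exclusions "Age <2 years and/or <10 kg of weight". A contact aged at least 2 years and weighing at least 10 kg passes this criterion. It sets no upper weight limit for any age.
- **Table 2** (Post-exposure prophylaxis) has four rows: 600 mg from age 15 years; 450 mg for ages 10–14 years; 300 mg for "6–9 years and body weight of ≥20 kg"; and 150 mg for "≥2 years old and body weight between 10–20 kg". The first two rows carry no weight condition. The last carries no upper age limit.

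The text introduces the table as the operative schedule: "The SDR-PEP dosages used in this project (table 2) are consistent with these WHO guidelines". The article gives no order in which the rows are to be read and does not say whether age or weight takes precedence.

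**The concern.** A dose table must return one answer for each person who is eligible to be dosed. Here the eligibility rule and the dose rows do not have the same boundaries. Two of the four rows use age alone and two combine age with weight, so the rows can leave a gap or overlap.

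What is at stake is safety and uniform practice. The drug goes to contacts without leprosy, many of them children. It is given at skin camps and health centres attached to 62 facilities (17 in Ethiopia, 22 in Mozambique, 23 in Tanzania; Randomisation section). Where the table gives no answer or two answers, different sites could handle the same child differently while each believes it is following the protocol.

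**Working it through.** No sample-size or power arithmetic applies. The check takes each eligible age and weight and counts the Table 2 rows that match.

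**Inputs.** Eligible: age ≥2 years and weight ≥10 kg (Table 1). Rows, read literally (Table 2):

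- R1: age ≥15 → 600 mg
- R2: age 10–14 → 450 mg
- R3: age 6–9 and weight ≥20 kg → 300 mg
- R4: age ≥2 and weight 10–20 kg → 150 mg

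Age is taken in completed years. The wording of R4 does not settle whether 20 kg itself belongs to it, so both readings were tried.

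**Reading A: R4 includes 20 kg**

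| Age (years) | 10 to <20 kg | exactly 20 kg | >20 kg |
|---|---|---|---|
| 2–5 | 150 | 150 | **no row** |
| 6–9 | 150 | **300 and 150** | 300 |
| 10–14 | **450 and 150** | **450 and 150** | 450 |
| ≥15 | **600 and 150** | **600 and 150** | 600 |

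**Reading B: R4 excludes 20 kg**

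| Age (years) | 10 to <20 kg | exactly 20 kg | >20 kg |
|---|---|---|---|
| 2–5 | 150 | **no row** | **no row** |
| 6–9 | 150 | 300 | 300 |
| 10–14 | **450 and 150** | 450 | 450 |
| ≥15 | **600 and 150** | 600 | 600 |

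A finer enumeration (ages 2 to 17 years, weights 10 to 60 kg in 0.5 kg steps) gave the same pattern under both readings.

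**Result.** The gap at ages 2–5 years and the overlap from age 10 years exist under either reading. Reading B removes the single-point overlap at ages 6–9 years but extends the gap to 20 kg.

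**Size of the conflict where two rows match.**

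- Ages 10–14: 450/150 = 3
- Ages 6–9 at exactly 20 kg: 300/150 = 2
- Ages ≥15: 600/150 = 4, but at a weight that is rare at that age

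**Number of contacts affected.** This cannot be computed. The article gives no age or weight distribution for contacts.

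**The case against.** **The rows have a natural order.** They run downward by age, with a low-weight row last. If staff take the first row that matches, every overlap disappears. That is a plausible way to read the table, but the article does not state it. It also leaves the gap untouched, because no order of reading supplies a row that is not there.

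**Working documents may settle it.** The Integrated skin screening section says that prophylaxis distribution follows SOPs, the Ethics section mentions an SOP on rifampicin administration, and training covers giving SDR-PEP. These documents are not shown and may be clearer. What the article says of them concerns the eligibility criteria and the emergency allergy kit; it does not say that they resolve the dose rows. So it would go too far to assert that field staff do in fact improvise. It remains true that the printed schedule gives no answer, or two, for some eligible contacts.

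**The table is said to follow WHO guidance.** That cannot be checked from the article. Even if correct, it would not close a gap or remove an overlap in the rows as printed.

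**Stronger readings that are not supported.**

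- A reader might infer that the table as a whole is unusable. It is not: outside the cells in bold, each eligible combination maps to one row.
- A reader might infer that a primary outcome, the number of contacts receiving SDR-PEP, is compromised. Where two rows match, the contact counts as having received SDR-PEP under either row. Only the gap could change the count. Both arms use the same table, the planned analysis of this outcome is descriptive, and planned screening is about 270 × 100 = 27 000 contacts against 405 × 6 = 2 430. A few children in the gap would not alter that contrast.
- A reader might want a head count. Any percentage applied to the roughly 30 000 planned contacts would be a guess.

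**Conclusion.** Wrong as written, for a limited set of contacts. Read with Table 1, Table 2 gives no dose row for children aged 2–5 years weighing more than 20 kg, and two rows differing threefold for contacts aged 10–14 years weighing 10–20 kg. The overlaps at exactly 20 kg for ages 6–9 years and at 10–20 kg from age 15 years are marginal.

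The gap and the main overlap hold whichever side of the boundary 20 kg falls on. The conclusion assumes only that the rows mean what they say and that no unstated precedence applies; an unstated precedence could remove the overlaps but not the gap. The point rests on dosing safety and consistency between sites, and not on bias in the comparison of the two interventions.

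**What to change.** Reconcile Table 2 with the age and weight criterion in Table 1 and with the rifampicin SOP, so that each eligible combination of age and weight falls in exactly one row. This needs boundaries that do not overlap, a clear assignment of 20 kg, and a stated precedence wherever age and weight point to different rows. If the SOP already does this, bring the published table into line with it. Which row or dose applies, and how the contacts now without a row are to be handled, is for the sponsor's clinicians to decide.

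The cost is one table correction and a matching note in the SOP and training material. Sample size, randomisation and analysis are unaffected.

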### Outcomes

The primary objectives of this study are to identify the most effective and feasible approach for screening contacts of patients with leprosy in combination with administering chemoprophylaxis to prevent leprosy (table 3). Because of the long incubation period of leprosy, it will not be possible to observe reduced transmission at the population level, in terms of a reduced new case detection rate, during this project period. The active case finding component and raised awareness, however, are expected to lead to more detected cases, improved early case detection and disability rates at time of diagnosis. We hypothesise that enhanced case finding and integrated skin screening will lead to an overall reduction of detection delay primarily in the community-based intervention over the study duration, driven by the diagnosis of patients with early signs of leprosy (and shorter delays) that would otherwise go undetected.

**Table 3 T3:** PEP4LEP project outcomes and methods of analysis

Objective	Outcome	Hypothesis	Outcome measure	Method of analysis
1.1 To compare the effectiveness of a skin camp prophylaxis intervention with a health centre-based prophylaxis intervention in terms of the rate of patients with leprosy detected and delay in case detection	Primary: Case detection delay	Reduction in case detection delay is expected to be greater in the community-based intervention compared with the health centre-based household contact approach	Number of months since first signs or symptoms of leprosy until diagnosis (including assessing both ‘patient delay’ and ‘health-system delay’); G2D percentage among newly diagnosed patients with leprosy	Descriptive statistics; multivariate models; non-parametric tests
	Primary: Number of contacts diagnosed with leprosy	The community-based intervention will identify more cases of leprosy from contact screening compared with the health centre household contact-based approach	Number of contacts diagnosed with leprosy; child proportion; female proportion; MB/PB classification of newly diagnosed patients with leprosy	Descriptive statistics; Pearson’s χ^2^ test; Fisher’s exact test; multivariate logistic regression analysis
	Primary: Number of contacts who received chemoprophylaxis	The community-based intervention will allow more contacts to be screened and receive SDR-PEP compared with the health centre-based household contact approach	Number of contacts screened; number of contacts who received SDR-PEP	Descriptive statistics
1.2 To compare the feasibility of the two chemoprophylaxis interventions (screening household contacts or screening contacts via skin camps) in terms of cost-effectiveness and acceptability	Secondary: Cost-effectiveness of each intervention	The community-based intervention will be more expensive but will have a greater impact compared with the health centre-based household contact approach	Number of index patients included; number of contacts screened; number of cases prevented; number of disabilities avoided; operational costs; out-of-pocket expenses	Health economic evaluations
	Secondary: Acceptability of each intervention	Both interventions will be accepted in participating countries	Number of index patients included; number of contacts screened; and qualitative outcomes	Descriptive statistics; qualitative content analysis of interviews; FGDs and potentially observations
2.1 To assess the acceptability of an integrated skin diseases approach and the use of the SkinApp	Additional: Number of contacts diagnosed with other skin diseases	The community-based intervention will identify more cases of other skin diseases from contact screening compared with the health centre-based household contact approach	Number of contacts diagnosed with skin diseases and with NTDs that manifest with skin lesions	Descriptive statistics; Pearson’s χ^2^ test; Fisher’s exact test; multivariate logistic regression analysis
	Additional: Acceptability of an integrated skin screening approach and the use of the SkinApp	The integrated skin screening approach will encourage screening participation, and the SkinApp will help health workers to diagnose skin diseases	Number of contacts diagnosed with skin diseases and with NTDs that manifest with skin lesions; utilisation of the SkinApp during contact screening; and qualitative outcomes	Descriptive statistics; sensitivity and specificity; positive and negative predictive values; qualitative content analysis of interviews, FGDs and potentially observations
2.2 To compare the capacity of health workers in diagnosing leprosy, other skin diseases and other NTDs that manifest with skin lesions before the start of the study with their capacity in the third year	Additional: Capacity of health workers in diagnosing leprosy and other skin diseases	Participation in training and the use of the SkinApp will improve health worker capacity	Results of health worker capacity assessments and qualitative outcomes	Descriptive statistics; qualitative content analysis of interviews, FGDs and potentially observations

FGD, focus group discussion; G2D, grade 2 disability; MB, multibacillary; NTD, neglected tropical disease; PB, paucibacillary; SDR-PEP, post-exposure prophylaxis with single-dose rifampicin.

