## Introduction

Leprosy, or Hansen’s disease, is a communicable disease caused by *Mycobacterium leprae* that is still a public health problem in many countries. It is formally recognised by the WHO as a neglected tropical disease (NTD).^1^ The annual reported number of newly detected patients with leprosy was 202 185 in 2019.^2^ If left untreated, leprosy potentially results in disability, which can have severe consequences such as stigma and poverty.^3^ Leprosy has a long and variable incubation time, ranging from 2 to 20 years, during which it is assumed that transmission can take place.^4^ The risk of developing leprosy is higher in household contacts and neighbours of patients than it is in the general community.^5^ Moet *et al* demonstrated that physical and genetic distance were independently associated with the risk of a contact developing leprosy.^6^ According to the WHO, contact screening should be offered to a person who has been in contact with an untreated leprosy index case for at least 20 hours per week during at least 3 months in the previous year.^4 7 8^ An index case is defined as a person diagnosed with leprosy for the first time.^7^

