#### Primary outcome measures

The primary outcome measures of effectiveness in the comparison of the two interventions are:

Case detection delay, measured in months since the first signs or symptoms of leprosy until diagnosis and in the number of patients with grade 2 disability.Number of new patients with leprosy, subdivided into child proportion, female proportion and multibacillary/paucibacillary classification.Number of contacts screened and receiving SDR-PEP.

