#### Secondary outcome measures

Feasibility will be assessed by looking at outcome measures related to cost-effectiveness and acceptability (table 3):

A cost-effectiveness analysis will be undertaken in the third year of the project, encompassing the costs incurred by the health system and the beneficiaries (out-of-pocket expenditure). It will include collecting indicators such as unit costs, costs per case detected, costs per disability-adjusted life years averted and costs per extra case found. The current practice ‘routine service provision’ will be compared with the two study interventions.The acceptability of both interventions will be determined by comparing the number of index patients and contacts included, as well as by using qualitative research methods, such as semi-structured interviews guided by topic lists, focus group discussions (FGDs) with relevant stakeholders and potentially ethnographic observations during the interventions for further data validation. More in-depth (country-specific) protocol descriptions on the acceptability and cost-effectiveness side-studies will be developed together with health economist(s) and social scientist(s).

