### Sample size

The sample size calculation was based on case detection delay as the main outcome measure for comparing the effectiveness of each intervention. This measure was used for the calculation because the epidemiological impact (ie, reduction in overall new case detection rate in PEP4LEP districts) will not become apparent within the study duration due to the long incubation time of leprosy. The mean or median delay will be compared between both interventions and with the baseline. A baseline case detection delay will be estimated in each country by interviewing recently diagnosed patients with leprosy with the same structured questionnaire prior to the start of the study. For the sample size calculation, a literature-based estimated average case detection delay of 24 months for patients with leprosy with a SD of 8 months was used, with the conservative assumption that a minimal delay difference of 3 months would be detected between both interventions.^73 74^ In order to achieve this, we aim to include at least 675 index patients in the study: 270 in the community-based intervention areas (30 per country per year) and 405 new patients in the health centre-based intervention areas (45 per country per year). Approximately 100 contacts will be screened per index patient in the community-based intervention areas, and approximately 6 contacts will be screened per index patient in the health centre-based intervention areas; thus, a total of approximately 30 000 contacts will be screened (figure 3). We expect no major differences in case detection delay between clusters and within clusters, hence no significant design effect is foreseen. For the feasibility study component and additional research objectives, interviews and FGDs are planned. For the interviews, a minimum of 10 index patients, 10 household contacts, 10–20 community contacts, 10 health workers/community volunteers, 4 health decision-makers and 10 community leaders will be included. For the FGDs, 6–10 participants will be included: two groups of index patients, two groups of household contacts, two groups of community contacts, two groups with health workers and one to two groups with decision-makers. Contacts refusing to receive skin screening and/or take SDR-PEP, but who are willing to participate in the qualitative study component and community members outside of the 20 closest houses to the index patient in intervention one will also be included. The qualitative research sampling will be purposive, according to the defined target groups, and balanced according to, for example, gender, age, education level, religion and/or socio-cultural background. All fully trained health staff involved in the PEP4LEP project will be asked to consent to enrol in the capacity assessment.

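### Table 3 hypothesises that skin camps find more leprosy cases, but the tests it lists compare the proportion of screened contacts diagnosed and can reject in favour of the other arm

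*Protocol article*

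**What the plan says.** Table 3 makes the number of contacts diagnosed with leprosy a primary outcome. Its hypothesis is that "The community-based intervention will identify more cases of leprosy from contact screening compared with the health centre household contact-based approach". The methods cell lists descriptive statistics, Pearson's χ² test, Fisher's exact test and multivariate logistic regression. The measures cell also names the child proportion, the female proportion and the multibacillary/paucibacillary (MB/PB) classification. Objective 1.1, in the same row, speaks of the rate of patients detected and gives no denominator. The Primary outcome measures section calls the outcome the number of new patients.

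The Sample size section plans 270 index patients in the camp arm and 405 in the health-centre arm. "Approximately 100 contacts will be screened per index patient in the community-based intervention areas", against about 6 in the other arm, and the total is put at about 30 000.

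The Introduction reports that "physical and genetic distance were independently associated with the risk of a contact developing leprosy". The section on the health centre-based intervention adds that leprosy clusters within households. According to Study design, camps screen household members and neighbours together.

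Two smaller points belong here. Table 3 also hypothesises that "The community-based intervention will allow more contacts to be screened and receive SDR-PEP compared with the health centre-based household contact approach", with descriptive statistics only. The Primary outcome measures section expresses detection delay partly "and in the number of patients with grade 2 disability", where Table 3 uses a percentage.

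**The concern.** The hypothesis and the tests answer different questions. The hypothesis asks which strategy finds more cases. A χ², Fisher or logistic comparison of diagnosed against not diagnosed contacts asks in which arm a screened contact is more likely to have leprosy. Camps add many neighbours, whose risk is expected to be lower, to the same kind of household contacts that the other arm screens. That dilutes the proportion in the camp arm even though every additional case is a gain.

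At stake is the reading of a primary outcome. The trial could report a significant result against camps for an outcome on which camps did what was hypothesised.

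**Working it through.** **Inputs from the Sample size section.** 270 index patients × 100 contacts = 27 000; 405 × 6 = 2 430. The sum is 29 430, which reproduces the stated total of about 30 000. The ratio of contacts is 27 000 / 2 430 = 11.1.

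**Assumptions, not in the article.** Each camp screens 6 household contacts and 94 neighbours. Yield per screened contact is h for household contacts (the same in both arms) and n for neighbours. Clustering is ignored unless stated.

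**Formulas.**
- Camp cases = 270 × (6h + 94n) = 1 620h + 25 380n.
- Health-centre cases = 405 × 6h = 2 430h.

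**Direction, by arithmetic alone.**
- The camp proportion is below the health-centre proportion whenever camps find fewer than 11.1 times as many cases.
- Under the assumptions, that condition is (6h + 94n)/100 < h, which reduces to n < h. The per-contact test then asks only whether neighbours have a lower yield than household contacts, which the article's own background leads one to expect.
- The raw camp count is higher unless n/h is below 810 / 25 380 = 3.2%.
- Cases per index patient are higher in camps for any n above zero.

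**Worked example, h = 2%, n = 0.5%.**
- Camps: 1 620 × 0.02 + 25 380 × 0.005 = 32.4 + 126.9 = 159.3 cases, or 0.59% of 27 000.
- Health centre: 2 430 × 0.02 = 48.6 cases, or 2.0% of 2 430.
- Odds ratio 0.29; uncorrected χ² gives p about 2×10⁻¹⁵, against camps.
- Per index patient: 159.3 / 270 = 0.59 and 48.6 / 405 = 0.12, a ratio of 4.9 in favour of camps.

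**Range** (expected counts, uncorrected χ²):

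| h | n | Cases, camp vs health centre | Odds ratio | p | Ratio of cases per index patient |
|---|---|---|---|---|---|
| 1% | 0.3% | 92.3 vs 24.3 | 0.34 | 8×10⁻⁷ | 5.7 |
| 1% | 0.5% | 143.1 vs 24.3 | 0.53 | 0.003 | 8.8 |
| 1% | 1% | 270.0 vs 24.3 | 1.00 | 1.0 | 16.7 |
| 2% | 0.3% | 108.5 vs 48.6 | 0.20 | 4×10⁻²⁵ | 3.3 |
| 2% | 0.5% | 159.3 vs 48.6 | 0.29 | 2×10⁻¹⁵ | 4.9 |
| 2% | 1% | 286.2 vs 48.6 | 0.52 | 3×10⁻⁵ | 8.8 |
| 3% | 0.3% | 124.7 vs 72.9 | 0.15 | 10⁻⁴⁸ | 2.6 |
| 3% | 0.5% | 175.5 vs 72.9 | 0.21 | 7×10⁻³⁴ | 3.6 |
| 3% | 1% | 302.4 vs 72.9 | 0.37 | 3×10⁻¹⁵ | 6.2 |

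Eight of the nine combinations are significant against camps. Dividing χ² by an assumed design effect of 3 leaves seven; 1%/0.5% becomes p = 0.09.

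**Where significance is lost.** At lower or closer yields the direction stays but significance does not: 0.5%/0.3% gives p = 0.12, 1%/0.75% gives p = 0.21, and 0.2%/0.1% gives p = 0.19.

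**The case against.** The strongest reply is that the article does not state the unit of analysis. The same cell covers the child, female and MB/PB proportions, for which χ², Fisher and logistic regression are standard, and the count may be meant for descriptive statistics alone. This stands in part, because the per-contact reading is an inference. It is the natural one, though. Objective 2.1 lists the same tests for an outcome whose only measure is a number of contacts diagnosed with other skin diseases. If the reading is wrong, the case-finding hypothesis has no test at all.

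A second reply is that the wider invitation is the intervention, so finding more cases is a legitimate programme result. That is right. A reader might infer that the counts are wholly fixed by design and therefore worthless. The documents do not support this: 100 and 6 are approximate planning figures, attendance and eligibility can fall short, and the counts feed the cost-effectiveness analysis. What the count needs is a denominator, since the arms plan 270 and 405 index patients.

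A reader might also extend the criticism to the other outcomes, where it is weak. The SDR-PEP outcome is descriptive, so no test can mislead there. On acceptability, the article says "The acceptability of both interventions will be determined by comparing the number of index patients and contacts included", but the same sentence adds qualitative methods, and the hypothesis is that both interventions are accepted. For grade 2 disability, Table 3 already uses a percentage. Case detection delay, not this outcome, drives the sample size.

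**Conclusion.** The point holds. For one primary outcome, the tests named do not test the stated hypothesis and can point the opposite way. That the health-centre arm has the higher proportion whenever camps find fewer than 11.1 times as many cases follows from the planned contact numbers.

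Significance rests on assumed yields, the 6 + 94 split and no clustering. Over yields of 1–3% in household contacts and 0.3–1% in neighbours, the odds ratio runs from 0.15 to 1.00, while cases per index patient are 2.6 to 16.7 times higher in camps. It would go too far to say that the test would reject against camps at every plausible yield. It does not at 1%/1%, nor at several lower or closer yields, and the article gives no yields. The p values would also be larger once health-centre clustering is allowed for.

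**What to change.** - Define the outcome once, as leprosy cases newly detected by contact screening per index patient, and use that definition in objective 1.1, Table 3 and the Primary outcome measures section.
- Compare arms with a count model, for example Poisson or negative binomial with log index patients as offset, that accounts for health-centre clustering and country. Other models for the same quantity would also serve. Report the ratio with its confidence interval: under the assumptions above its direction is largely expected, so its size is what informs.
- Keep χ², Fisher and logistic regression for the child, female and MB/PB proportions, and say so.
- Add a comparison restricted to household contacts in both arms as a like-for-like secondary analysis.
- Minor: give grade 2 disability as a percentage throughout, and report contacts screened and given SDR-PEP with their denominators, since the raw counts largely reflect the planned sizes.

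The cost is a change of wording, slightly more analysis work, and recording whether each camp contact belongs to the index patient's household. Sample size and conduct are otherwise unaffected.
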